# Effectiveness and safety of electroacupuncture for poststroke patients with shoulder pain: study protocol for a double-center, randomized, patient- and assessor-blinded, sham-controlled, parallel, clinical trial

**DOI:** 10.1186/s12906-019-2468-x

**Published:** 2019-03-12

**Keywords:** Stroke, Shoulder pain, Electroacupuncture, Randomized controlled trial

## Abstract

**Background:**

Practitioners of complementary and alternative medicine have suggested that acupuncture could alleviate poststroke shoulder pain, based on the clinical evidence. This study protocol is aimed at showing the effectiveness and safety of electroacupuncture therapy for stroke survivors with shoulder pain.

**Methods:**

After assessing their eligibility, 60 stroke survivors with shoulder pain will be enrolled from two traditional Korean medicine hospitals and randomly divided into either the verum or the sham electroacupuncture (EA) group with a 1:1 ratio. The participants will receive 9 sessions of EA procedures for 3 weeks. The verum EA consists of needling on 6 unilateral acupoints (LI4, LI15, TE14, SI9, SI11, and GB21) with electronic stimulation. A non-penetrating Park sham device and fake electronic stimulation will be used in the sham group on the same acupoints. Patients and outcome assessors will be blinded throughout the entire study. A visual analog scale will be used primarily for the evaluation, and pain rating scale, Fugl-Meyer assessment for upper extremity, modified Ashworth scale, manual muscle test, passive range of motion test, Korean version of a modified Barthel index, and Korean version of the Beck depression inventory will be also be measured. A blinding index will be assessed. For safety, adverse events will be recorded. Data will be statistically analyzed by two-sample t-test or Wilcoxon rank sum test for efficacy and a chi-squared test or Fisher’s exact test for safety, at 5% of significance level.

**Discussion:**

We expect this double-center, randomized, sham-controlled, patient- and assessor-blinded parallel trial to explore the effectiveness and safety of EA therapy, compared with sham EA, for poststroke shoulder pain.

**Trial registration:**

https://clinicaltrials.gov/ct2/show/NCT03086863

## Background

Hemiplegic shoulder pain (HSP) is a common complication of stroke survivors. It is estimated that HSP occurs in 16 to 84% of stroke patients [1] or 22 to 23% of the general population [2]. Due to HSP, poststroke patients may have difficulty with activities of rehabilitation and a deteriorated quality of life [3], which is why management or treatment of HSP is considered important.

Various conditions, such as structural injury from glenohumeral subluxation, capsular contractures, or rotator cuff disorders, are known to cause the pain [3]. It is specifically stated that impingement syndrome, brachial plexus injury, frozen shoulder, poststroke central pain, shoulder hand syndrome, myofascial pain syndrome, tendinitis, or bursitis could be related to the poststroke shoulder pain [4]; therefore, several curative methods have been applied and studied.

An evidence-based clinical practice guideline for stroke rehabilitation in Korea recommended shoulder support systems, physiotherapy, analgesics, intraarticular steroid injection, or botulinum toxin A (BTX-A) [5]. However, systematic reviews have discussed the pros and cons of intramuscular neuromuscular electric stimulation [3, 6], steroid injection [3, 6], BTX-A injection [3, 6, 7], shoulder supports [3], and even analgesia [3], which suggests that the treatments for HSP are controversial and inconsistent.

Practitioners in the field of complementary and alternative medicine suggest that acupuncture therapy can alleviate poststroke shoulder pain according to the evidence from systematic reviews and meta-analyses [8–10]. However, it fell short of the adequate randomized controlled trials (RCTs) and did not have the study quality or numbers to prove the effect of electroacupuncture (EA) therapy for HSP [10].

The objective of this study protocol is to conduct a double-center, randomized, patient- and assessor-blinded, sham-controlled, parallel clinical trial in order to show the effectiveness and safety of EA therapy for stroke survivors with HSP.

## Methods/design

### Aim, design, and setting of the study

#### Primary objective and study hypothesis

This clinical trial is primarily aimed at evaluating the effectiveness and safety of 3-week EA therapies, compared to sham comparator, for patients with shoulder pain that is rated on the visual analog scale (VAS) as ≥4 after a stroke, such as an intracerebral hemorrhage or infarction. The alternative hypothesis is that the mean difference in VAS for HSP, from baseline to endpoint, of the verum group is not equal to that of the sham group.

#### Secondary objectives

This study will also evaluate the effects of EA on a) physical performance, spasticity, muscle strength, and range of motion in shoulder joints, b) activities of daily living, and c) depression of stroke survivors, using intergroup/intragroup comparisons of various validated scales.

#### Study design

This clinical study is a double-center, randomized, sham-controlled, patient- and assessor-blinded, and parallel trial. A total of 60 stroke survivors will be given both verbal and written forms of in-depth information about the trial by traditional Korean medicine (TKM) doctors before participation. All participants will voluntarily sign the informed consent that has been approved by the ethics committee prior to enrollment. Prior to allocation, the enrolled participants will be screened by the eligibility criteria.

After being randomly allocated into either the verum or sham EA group, in a 1:1 of allocation ratio, the participant will receive 9 sessions of verum or sham EA procedures for 3 weeks (3 sessions a week). The acupuncture regimen consists of 6 unilateral acupoints (LI4, LI15, TE14, SI9, SI11, and GB21) with electronic stimulation. Patients and outcome assessors will be blinded from the beginning of the study through completion.

The overall schematic chart and study schedule are shown in Figs. 1 and 2, respectively.

**Fig. 1 Fig1:**
[figure not shown]
Schematic chart of the overall study. The template is from the CONSORT 2010 flow diagram. *EA* electroacupuncture, *VAS* visual analog scale, *PRS* pain rating scale, *FMA-UE* Fugl-Meyer assessment upper extremity, *PROM* passive range of motion, *MMT* manual muscle test, *MAS* modified Ashworth scale, *K-MBI* Korean version of modified Barthel index, *K-BDI* Korean version of Beck depression inventory, *BI* blinding index, *FAS* full analysis set, *PPS* per protocol analysis set, *SAS* safety assessment set

**Fig. 2 Fig2:**
[figure not shown]
Study schedule of enrollment, interventions, and assessments. The template is from the SPIRIT 2013 statement [11]. *VAS* visual analog scale, *PRS* pain rating scale, *FMA-UE* Fugl-Meyer assessment upper extremity, *PROM* passive range of motion, *MMT* manual muscle test, *MAS* modified Ashworth scale, *K-MBI* Korean version of modified Barthel index, *K-BDI* Korean version of Beck depression inventory

#### Setting and recruitment

Two TKM hospitals (Kyunghee University Korean Medicine Hospital, Seoul; Wonkwang University Gwangju Medical Center, Gwangju) in the Republic of Korea will recruit eligible participants. Both hospitals will post study advertisements online (webpage) and offline (posters) to enroll inpatients. To enhance recruitment, investigators will also monitor feasible medical records.

#### Ethical review and general statements

This trial protocol (version 1.5), including the informed consent forms, has been peer-reviewed and approved by the funder and the Institutional Review Board at Kyung Hee University Korean Medicine Hospital (approval No. KOMCIRB-170215-HR-002) according to the scientific content and ethical compliance with regulations, i.e., Good Clinical Practice and relevant laws by Ministry of Food and Drug Safety in Korea. The study has also been registered at ClinicalTrials.gov in March 2017 (identification No. NCT03086863).

We designed this interventional research at full length following the Standard Protocol Items: Recommendations for Interventional Trials (SPIRIT) 2013 statement [11] and Revised Standards for Reporting Interventions in Clinical Trials of Acupuncture (STRICTA): extending the CONSORT statement [12, 13].

### Eligibility criteria

#### Inclusion criteria

We will include any man or woman who a) is 19 years of age or older; b) was diagnosed with cerebral hemorrhage or infarction through an examination using computed tomography (CT) magnetic resonance imaging (MRI) at least 2 weeks prior to the enrollment; c) has hemiplegic shoulder pain with a VAS score ≥ 4; d) agrees that any treatments, including analgesics, for HSP will not be changed from the previous 2 weeks prior to the enrollment until the last evaluation, if applicable; and e) has received a full explanation about the research and has given informed consent.

#### Exclusion criteria

Participants will be excluded if they have/had a) disorders, traumatic injury, or surgery of shoulders even before their stroke; b) pacemakers, embedded neural stimulator, cardiac arrhythmia, epilepsy, peripheral neural injury on their medical history; c) psychiatric disorders; d) cancer within the past 5 years, regardless of its prognosis and location; e) cognitive impairment that interferes with clinical assessment; f) hypersensitivity to or fear of acupuncture; g) bleeding disorders (e.g. hemophilia or von Willebrand disease, etc.), h) a pregnancy, i) difficulty in communicating with researchers, or j) any other conditions that are considered inappropriate for participating in the trial by experienced practitioners.

#### Dropout criteria

Any participant will be dropped from the study if he or she a) has a belated discovery of any ineligible criteria; b) withdraws consent, wants to cease, or refuses to undergo the EA or sham procedures; c) is lost to follow-up; d) shows serious adverse events and fails to maintain the protocol; e) takes concomitant use of the prohibited drugs or therapies (see the section, Concomitant treatments); f) violates the protocol seriously; or g) is considered inappropriate to keep in the trial by investigators’ clinical experience.

### Randomization and allocation

Random numbers will be generated by an independent statistician ([name]) using SAS® 9.4 software (SAS Institute Inc., North Carolina, USA). Block randomization with randomly selected block sizes of either 2 or 4 will also be adopted to keep the number of participants in each group as equal as possible at all times with an allocation ratio of 1:1. Of the 60 total participants, 40 will be stratified by site subgroups (20 in Kyunghee University Korean Medicine Hospital and 20 in Wonkwang University Gwangju Medical Center, respectively) and the remaining 20 will be competitively recruited from both sites.

Sealed and opaque envelopes with random numbers will be prepared by the statistician and opened by a study coordinator after eligibility assessment. Participants will be allocated into either the verum or sham EA group in the order of giving the informed consents. The study coordinator will notify the allocated group to practitioners, who will be different from outcome assessors.

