### Statistical analysis

A full analysis set is defined as a group of participants who receive 7 or more verum or sham EA sessions with an evaluation of the primary outcome at the endpoint, while a per protocol set is a subset of participants who complete all verum or sham EA sessions as planned in the protocol. We are going to statistically analyze the obtained data, primarily on the full analysis set, as well as, on the per protocol set for the efficacy analysis. Missing values will be imputed by the method of last observation carried forward in the full analysis set.

Demographic information will be tested with a two-sample t-test or Wilcoxon rank sum test for continuous variables and chi-squared test or Fisher’s exact test for categorical variables. When statistically significant differences between groups are found in demographic information, especially age and sex, those will be used as covariates for effectiveness analysis.

Primary and secondary variables will be summarized using the mean ± standard deviation and tested by two-sample t-test or Wilcoxon rank sum test depending on normality of the distribution. If concomitant treatments are significantly different between groups, intergroup effect will be tested by an analysis of covariance with the information of concomitant treatments adjusted. For the intragroup effect, the results of the VAS scores will be tested by paired t-test or Wilcoxon signed rank test. The significance level will be set at 0.05 (two-sided). Statistical analyses will be performed using SAS® 9.4 software (SAS Institute Inc., North Carolina, USA) by an independent statistician ([name]).

The number of adverse events will be presented with a 95% confidence interval on a safety set defined as a subset of participants who receive at least one verum or sham treatment. A chi-squared test or Fisher’s exact test will be carried out to compare the significant differences between groups.

The results of the blinding assessment will be presented as the number of participants per group assignment with the participants’ deductions of their group assignment in a 2 × 3 table. We will consider blinding to be successful in this study if the calculated confidence interval of the new BI includes zero, following the previous study [14].

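### Randomisation is stratified by site but the efficacy tests ignore site, so any between-site variance stays in the error term

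*Protocol article*

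**What the plan says.** The Randomization and allocation section of the protocol article states: "Of the 60 total participants, 40 will be stratified by site subgroups", with 20 at each of the two hospitals, and "the remaining 20 will be competitively recruited from both sites". It adds: "Block randomization with randomly selected block sizes of either 2 or 4 will also be adopted", to keep the groups "as equal as possible at all times with an allocation ratio of 1:1". Allocation follows consent order: "Participants will be allocated into either the verum or sham EA group in the order of giving the informed consents". No stratification factor other than site is named. The text does not say whether the 20 competitive places are filled from lists held separately at each site.

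The Statistical analysis section has primary and secondary variables "tested by two-sample t-test or Wilcoxon rank sum test depending on normality of the distribution". Covariates can enter by two routes only, and both depend on a significant difference between the arms. For demographics: "When statistically significant differences between groups are found in demographic information, especially age and sex, those will be used as covariates". For concomitant treatments: "intergroup effect will be tested by an analysis of covariance with the information of concomitant treatments adjusted". Site appears in neither route, nor anywhere else in that section.

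**The concern.** Randomising within sites holds the arms balanced on site. The true sampling variance of the treatment difference then contains little or no between-site component. A two-sample test that ignores site still counts the between-site variance when it estimates its standard error. If the hospitals differ in mean VAS change, the standard error comes out too large, the p-value too large and the confidence interval too wide. The benefit of stratifying is paid for in the design and given up in the analysis.

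The conditional covariate rules do not repair this. Even if site were treated as a demographic variable, stratification is meant to keep the arms alike on site, so a trigger that needs a significant difference would hardly ever fire.

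At stake is some precision on the primary endpoint in a trial sized at 24 evaluable participants per arm.

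**Working it through.** **Inputs.** From the Power calculation section: VAS reductions of 3.52 (SD 2.67) and 1.38 (SD 2.43), two-sided alpha 0.05, power 0.8, 24 per group, 20% dropout, 60 in total. From Randomization and allocation: random blocks of 2 or 4, ratio 1:1, 20 per site plus 20 competitive. The share f of the variance of VAS change that is due to site is not in the documents. It is an assumption, shown over 0% to 20%.

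**Step 1: the plan's own figure.** Difference = 3.52 − 1.38 = 2.14. Pooled SD = √((2.67² + 2.43²)/2) = √6.517 = 2.553. Standardised effect = 2.14/2.553 = 0.838. The normal approximation gives 22.3 per group; the t distribution gives 23.34, rounded up to 24. Then 24/0.8 = 30 per group, 60 in total. The stated figures reproduce. The power of the t-test at 24 per group is 81.1%.

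**Step 2: power with site in the model, 24 per arm.** The residual SD is 2.553·√(1 − f). The noncentrality is 2.14/(2.553·√(1 − f)·√(2/24)) = 2.904/√(1 − f), on 2 × 24 − 3 = 45 degrees of freedom (46 for the unadjusted test). The 2.553 is treated as the total SD, between-site variation included.

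| Assumed f | Noncentrality | Fall in SE | Power with site |
|---|---|---|---|
| 0% | 2.90 | 0% | 81.1% |
| 5% | 2.98 | 2.5% | 83.0% |
| 10% | 3.06 | 5.1% | 85.0% |
| 15% | 3.15 | 7.8% | 86.9% |
| 20% | 3.25 | 10.6% | 88.8% |

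At f = 0 the lost degree of freedom leaves power at 81.1% to one decimal.

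**Step 3: both analyses on the same trials.** Step 2 compares adjusted power with the planned value. Under stratification the unadjusted test also moves a little, so the two analyses were simulated together: 60 analysed, 6,000 trials per scenario. In one version all 60 come from site-specific lists. In the other, the last 20 come from one shared list.

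| f | Lists for the last 20 | Type I error without / with site | Power without / with site |
|---|---|---|---|
| 0% | site-specific | 4.8% / 4.8% | 88.8% / 88.7% |
| 0% | shared | 5.3% / 5.2% | 89.1% / 89.0% |
| 5% | site-specific | 4.3% / 4.7% | 89.7% / 90.6% |
| 5% | shared | 4.4% / 4.8% | 89.4% / 90.2% |
| 10% | site-specific | 4.1% / 5.2% | 90.1% / 91.6% |
| 10% | shared | 3.9% / 4.4% | 89.1% / 91.2% |
| 20% | site-specific | 2.8% / 4.8% | 91.3% / 94.5% |
| 20% | shared | 3.6% / 4.8% | 91.0% / 94.5% |

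The Monte Carlo standard error of a 5% rate is √(0.05 × 0.95/6000) = 0.28 percentage points. Ignoring site makes the test conservative as f grows, whichever lists are used. With 60 analysed, the power gained by including site is about 1 point at f = 5%, 1.5 to 2 at 10% and 3 to 3.5 at 20%.

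**The case against.** **The gain may be nil.** The documents give no site variance share. The endpoint is change from baseline, so a stable difference in pain level between hospitals cancels, and the procedure is standardised. A small f is plausible, and at f = 1% power at 24 per arm rises only to 81.5%. This stands, and it limits the size of the point.

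**It could be left to the SAP.** An analysis plan may exist and may add site. But the article does not stay silent: it names an unadjusted test and lists the conditions under which covariates enter. A plan that added site would change the published primary test.

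**There is no model to add a term to.** The default analysis is a t-test or a rank test, and a fixed effect does nothing for the rank test. This stands, so the remedy has to cover both branches.

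**A stronger reading is tempting.** A reader might infer that a third of the sample is randomised outside the site strata, from one sequence shared between two cities, so that envelopes are opened out of order and blocks are broken. The article does not say so. Competitive recruitment can describe an enrolment quota, with site-specific envelopes throughout, and such logistics are commonly left to the full protocol. Nor does the article state that practitioners and assessors differ by site.

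Even on the shared-list reading the effect is modest. If ten of the 20 came from each site off one balanced list, the chance of a 7:3 or worse split within a site would be 2 × (14400 + 2025 + 100 + 1)/184756 = 17.9%. Added to a balanced first 20, a 7:3 split gives 17:13 of 30. The arms then differ in site mix by 17/30 − 13/30 = 0.133. A site share f corresponds to a difference between sites of 2√f × 2.553, which is 1.14 at 5% and 1.98 at 15%. The estimate would shift by 0.133 × 1.14 = 0.15 to 0.133 × 1.98 = 0.26 VAS points, against a planned difference of 2.14.

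**Conclusion.** The point holds as one of efficiency and consistency. The trial stratifies by site, explicitly for 40 of 60, and then specifies tests that ignore site. If site explains 0%, 5%, 10% or 15% of the variance of VAS change, a site-adjusted analysis has power of about 81%, 83%, 85% or 87% at 24 per arm. These figures rest on the assumed shares and on taking the earlier study's pooled SD as the total SD here.

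A reader might infer that the primary test is invalid or the sample size wrong. Neither follows. Ignoring site does not inflate type I error: in the simulation it fell below 5% wherever site mattered. Chance imbalance between sites is already covered by the error rate of the unadjusted test, and the stated 24 per group and 60 in total reproduce. Nor is it established that stratification is incomplete; the wording on the last 20 is unclear and needs one clarifying sentence.

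**What to change.** - **Analysis.** Prespecify a linear model for VAS change with treatment and site as fixed effects, and the same form for the secondary outcomes. Where the Wilcoxon rank sum test would have been used, name the site-stratified van Elteren test. Keep site in any analysis of covariance that the conditional rules bring in. The cost is one degree of freedom (46 to 45 at 24 per arm).
- **Randomisation.** State that all 60 participants are randomised from site-specific blocked lists, with enough envelopes at each site for its share of the competitive 20. At most that is 20 + 20 = 40 per site, or 80 envelopes in place of 60.
- **If enrolment has begun.** Adopt the site adjustment alone, documented before unblinding, and report how the last 20 were in fact allocated.

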### Blinding

We will use the non-penetrating Park-sham apparatus as a comparator. The same guide tube from the Park-sham needle will be used in both groups and, simultaneously, a fake noise from an identical electrical stimulator will be generated to maintain blinding during the procedures (see the section, Sham electroacupuncture). In addition, outcome assessors will be blinded, who are different from the study coordinators, TKM doctors performing the acupuncture procedures, and statistician. Unblinding before completing the study will only be allowed in cases of medical emergencies induced by serious adverse events (SAEs). At the end of the study, patients and outcome assessors, respectively, should try to deduce which group they thought to belong to. These answers will be used to calculate the new blinding index (BI) to evaluate success or failure of blinding [14].

### Verum electroacupuncture

The detailed procedures of EA are described following the STRICTA 2010 checklist [12, 13].

The regimen of EA therapy is composed based on the TKM’s theory on acupuncture and the clinical experiences of the TKM experts. All the patients in the verum EA group will go through an identical procedure. On the six adjacent acupoints (LI4, LI15, TE14, SI9, SI11, and GB21), placed on only the side with HSP, the acupuncture needles (stainless steel, 0.25 mm × 40 mm, Dong Bang Acupuncture Inc., Republic of Korea) will be inserted at a depth of 10–15 mm and the de qi sensation will be elicited. Park sham guide tubes will be also used in the verum EA group to blind the patients. The locations of each acupoint conforms to the standard defined by the World Health Organization [15]. Subsequently, a low frequency electronical stimulate (STN-111, Stratek, Republic of Korea) will be connected to the tips of needles to provide electrical stimulation at a medium frequency (30 Hz). Needles with electrical stimulation will be retained for 20 min.

Patients should undergo this procedure 3 times a week for 3 weeks (9 sessions in total). During the procedures, the practitioners are not allowed to talk to patients, minimizing other effects. The practitioners will be licensed TKM doctors with at least 1 year of clinical experience. These practitioners cannot assess the outcomes because assessors should remain blinded throughout the whole study.

